#### 20.12f Compliance of self-report tool

We will use linear multivariate regression analysis to model the difference in mean compliance rates for the Distress Thermometer self-report tool. The interventions (Distress thermometer and MH&A) will be included as well as a variable for their interaction effect. We will also include time period (year-quarter) and an interaction term between the time period and each intervention (Distress thermometer and MH&A).

# 21 Monitoring

There will be no data management or trial management committee, interim analysis or premature termination of the study.

# 22 Harms

Adverse events that are anticipated among this study population include, but are not limited to, program drop-out, failure to satisfy the criteria for program completion, ill health or hospitalizations due to substance abuse and mental health crises. These events will not be reported to the Research Ethics Board unless the investigators feel that the event may have been caused by the protocol procedure.

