# 12 Outcomes

## 12.1 Primary outcome measures

### 12.11 Program attendance

Difference in proportion of absence-free program days (AFDs) at 12 weeks from the start date of the TDTP, where ***absence-free days are defined by the cumulative number of days of program attendance during the 12-week study period.*** The potential number of AFDs for each apprentice is the cumulative number of program days that the apprentice is alive during the 12-week TDTP, with a maximum of 48 days (=12 weeks x 4 days/week). A day is defined as an 8–10-hour work-day during the TDTP from Monday to Thursday. An apprentice is considered to have attended a work-day as long as the Case Manager or their construction supervisor documents their attendance.

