### 12.12 Program completion

Difference in proportion of drop-outs at 12 weeks from start date of TDTP, where ***a drop-out is defined as an apprentice who fulfils any of the following criteria:***

- Has missed more than 50% of training days, or
- Who has elected to leave the program for reasons other than taking another job or returning to school

The proportion of drop-outs is defined as the ratio between the cumulative number of apprentices who meet the criteria for drop-out relative to the cumulative number of apprentices enrolled in the TDTP.

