# 17 Masking

This is an open-label, pragmatic study so neither study participants nor Community Builders® nor study personnel, including data analysts, will be masked to the allocation.

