### 18.14 Healthcare utilization

This data (see Section 12.22) is available from the Registered Persons Database, Ontario Mental Health Reporting System, Discharge Abstract Database, and National Ambulatory Care Reporting System through the Institute for Clinical Evaluative Sciences using a data linkage with each patient’s unique Ontario Health Insurance Plan number.

As a prescribed entity under the Personal Health Information Protection Act (27), the Institute for Clinical Evaluative Sciences is authorized to collect personal health information from health organizations without consent for the purposes of evaluation and monitoring of Ontario’s health system. The Institute for Clinical Evaluative Sciences is prohibited, under its agreements

with data providers, from contacting individuals whose information has been

entrusted to the Institute for Clinical Evaluative Sciences. This contractual obligation restricts any opportunity to seek individuals’ consent for use of their information for research.

The Institute for Clinical Evaluative Sciences will make available a research-ready, linked and risk-reduced coded dataset to the study investigators. Although highly de-sensitized, the research data is presented at an individual level. Study investigators will access the Research Data remotely on a secure, encrypted VMware virtual desktop called the Institute for Clinical Evaluative Sciences Data & Analytic Virtual Environment (IDAVE). Study investigators will perform analyses on IDAVE using statistical software. Research Data may not be copied or transferred from IDAVE. Only results derived from the Research Data that have been vetted for

re-identification risk and approved by Institute for Clinical Evaluative Sciences may be released from IDAVE.

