# 24 Ethics approval

This protocol and appendices will be reviewed and approved by the RVH Research Institute and the Clinical Trials Ontario-accredited RVH Research Ethics Board with respect to scientific content and compliance with applicable research and human subjects’ regulations.

The protocol, informed consent form, participant education and recruitment materials, and other requested documents, and any subsequent modifications, also will be reviewed and approved by the RVH Research Ethics Board.

Subsequent to initial review and approval, the RVH Research Ethics Board will review the protocol at least annually. The Principal investigators will make progress reports to the RVH Research Ethics Board at least annually and within three months of study termination. These reports will include the total number of participants enrolled, completed the study, in follow-up, lost-to-follow-up, and withdrawn; protocol and informed consent deviations and modifications; and if applicable, total number of adverse events.

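### Section 22 counts a primary outcome as an adverse event and filters ethics-board reports by unmasked attribution, and the one unfiltered comparison of crises (12.22) mixes harm with access to the MH&A service

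*Protocol*

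**What the plan says.** Protocol Section 22 names the anticipated adverse events as "program drop-out, failure to satisfy the criteria for program completion, ill health or hospitalizations due to substance abuse and mental health crises" and says that they "will not be reported to the Research Ethics Board unless the investigators feel that the event may have been caused by the protocol procedure". Section 17 states that neither participants, nor the training provider, "nor study personnel, including data analysts, will be masked to the allocation". Section 21 reads: "There will be no data management or trial management committee, interim analysis or premature termination of the study".

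Section 24 requires progress reports to the Research Ethics Board at least once a year and after the study ends. Their contents include enrolment and withdrawal counts "and if applicable, total number of adverse events".

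Two outcomes overlap with the Section 22 list:

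- Primary outcome 12.12 is the "Difference in proportion of drop-outs at 12 weeks from start date of TDTP". Section 20.11b models it as one binary variable, completion against drop-out.
- Secondary outcome 12.22 counts healthcare days over the 12-week program. Emergency visits, mental health and addictions outpatient visits, and acute, mental health or detoxification admissions all go into one count. Section 18.14 takes the data from linked administrative sources, including the "Discharge Abstract Database, and National Ambulatory Care Reporting System". Section 20.12b models the count by Poisson regression with terms for both interventions and their interaction.

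**The concern.** A harms section should let a reader see whether daily distress screening, or the referral route to the MH&A service, goes with more or fewer serious events. Three features work against this.

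1. A list that puts an efficacy endpoint beside hospital admissions gives a total that says little about harm.
2. Whether an event reaches the board turns on the opinion of people who know the allocation, and that opinion has something to attach to mainly where an intervention was delivered.
3. Two sections give the same board different instructions on what it receives.

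Section 30 plans wider use of the interventions if they prove superior, so the harms side of that decision should be readable.

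**Working it through.** Section 22 gives no figure to reproduce. The check sets its text beside the sections that it touches, with one small calculation.

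**1. Section 22 list against the primary outcomes.**

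| Section 22 event | Where else it appears |
|---|---|
| Drop-out | Primary outcome 12.12, coded 0 in 20.11b |
| Failure to meet completion criteria | The same outcome, 12.12 |
| Ill health or hospitalisation | Partly in secondary outcome 12.22 |
| Mental health crisis | Partly in 12.22, if it led to a registered visit or admission |

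The other primary outcomes, attendance (12.11: "Difference in proportion of absence-free program days (AFDs) at 12 weeks") and employment (12.13), are not on the list. So one of three primary outcomes is also an adverse event, named twice.

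**2. Size of the overlap.** Inputs: 400 apprentices (14.1) and historical completion of 75–80% (14.2). Assumption: everyone who does not complete counts as a Section 22 event.

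- 400 × (1 − 0.80) = 80
- 400 × (1 − 0.75) = 100

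If the Section 24 total means all adverse events, drop-out alone contributes 80 to 100. If it means attributed events only, and no drop-out is attributed, drop-out contributes none. The two readings can therefore differ by 80 to 100 from this source alone.

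**3. Where attributed reports can come from.** Under 5.3, BCM is the current standard of case management in Sudbury, with neither the tool nor the MH&A service. Sections 15 and 16.3 describe study introduction and consent only for cohorts allocated to the tool. An investigator who knows the allocation has little in a BCM cohort to which an event could be attributed. The filter is thus uneven across groups, and reports will come mainly from intervention cohorts whatever the true event rates.

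**4. Section 22 against Section 24.** Section 22 withholds unattributed anticipated events from the board. Section 24 gives the board a total. The qualifier in Section 24 does not say which events are counted.

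**5. Whether 12.22 can stand in.** Write a group's healthcare days as T = E + A + O, with E for emergency days, A for admission days and O for outpatient days. The between-group difference is ΔT = ΔE + ΔA + ΔO. Under 11.2 the MH&A intervention books appointments within 24 to 48 hours of referral, including at an addictions clinic, so it raises O by design. A positive ΔT may come wholly from ΔO (better access) or from ΔE + ΔA (more crises). A fall in E + A may be hidden by a rise in O. The planned model estimates an effect on T only. Deaths enter only as shorter exposure, because both the outcome and the exposure are defined while alive.

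**The case against.** The strongest reply is that Section 22 governs reporting to the ethics board, not collection, analysis or publication. Outcome 12.22 counts visits and admissions from administrative records with no causality judgement, 20.12b compares them between groups, and Section 31 commits to publishing whatever the direction. That stands. A reader might infer that harms cannot be compared between arms at all, but the documents do not support this. The limit is that the existing comparison cannot separate harm from access.

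Three other strong readings also go too far:

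- **Two primary outcomes on the list.** Drop-out and non-completion are the two sides of 12.12, so there is only one.
- **Zero attributed events in BCM by construction.** The protocol does not define its protocol procedures and excludes no group. The foundational-skills survey (18.13a) is for each apprentice. Attribution in BCM is unlikely, not impossible.
- **Section 21 contradicts Sections 24 and 27 on early termination.** The later sections use ordinary close-out and record-retention wording. Neither plans an early stop.

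It can also be said that Section 22 concerns notification of single events and Section 24 a periodic aggregate. That reading is possible, but the text does not state it, and staff would have to guess. Finally, table layouts are often left to an analysis plan. That is fair, so the point rests on what Sections 12.22, 22 and 24 themselves state, not on a missing table.

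**Conclusion.** The point holds in a limited form. Section 22 lists one primary outcome as an adverse event and makes ethics-board reporting of admissions and crises depend on unmasked attribution. It must be reconciled with the adverse-event total in Section 24. The only unfiltered between-group comparison of crises, 12.22, pools them with visits that the MH&A service generates.

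The measurable part is the 80 to 100 drop-outs that an unfiltered total would contain. This assumes that historical completion carries over to the trial and that completion there matches 12.12. The protocol gives no crisis or admission rate, so the distortion in the serious events cannot be sized.

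No planned efficacy analysis is affected, since drop-out is analysed once, under 20.11b. The change is worth making before results are known, but the defect does not undermine the trial.

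**What to change.** 1. In Section 22, take drop-out and non-completion off the adverse-event list. Section 12.12 already analyses them.
2. From the 18.14 linkage, tabulate deaths, emergency visits and admissions by group, regardless of attribution and separately from outpatient visits. Give the number and proportion of apprentices affected. Show investigator attribution as an extra column.
3. State in Sections 22 and 24 which count goes into the periodic report.

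**Conditions.** Consent (16.3) and demographic entry (19) are tied to the tool, so the protocol should say how cohorts without it are linked. The follow-up window must be reconciled: 12.22 gives the 12-week program, while the registration table in Section 1.1 adds 24 weeks afterwards.

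**Limits.** The table will not be perfectly clean. Section 11.2 itself sends apprentices at high risk of suicide to the emergency department. The MH&A service exists only in Barrie, so that contrast is also one between sites. Crises without a registered visit stay uncounted.

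**Cost.** Protocol wording and one table from a linkage already budgeted at 15 000 (Section 34). Linked data arrive late, so annual totals would rest on events known to study staff until the final linkage. No new committee is needed.

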# 23 Auditing

## 23.1 Investigator responsibilities

The investigators agree to perform the clinical trial in accordance with this clinical trial protocol, International Council for Harmonisation guideline for Good Clinical Practice (<https://ichgcp.net/>) and all applicable regulatory requirements.

## 23.2 Coordinating centre responsibilities

The RVH Research Institute will be responsible for taking all reasonable steps to ensure proper conduct of the clinical trial protocol.

## 23.3 Site initiation

Prior to the initiation of the study at each study site, the RVH Research Institute will be responsible for providing adequate training to the case managers, healthcare providers and study personnel. The training will cover all aspects of the study protocol and procedures and will include practical training on the use of the randomisation system, electronic case report forms and study materials such as the Distress Thermometer. The site initiation visit will be conducted by either teleconference, video conference or face-to-face meetings at the participating study site. Written and electronic materials will be supplied for study personnel and for the education of the case managers and healthcare providers at each site.

## 23.4 Study monitoring

An independent study monitor from the RVH Research Institute will visit each participating site biannually during the study period. This will ensure that the study is conducted according to the protocol, good clinic practice guidelines and relevant regulatory requirements. The main duty of the study monitor is to help the principal investigators and the RVH Research Institute maintain a high level of ethical, scientific, technical and regulatory quality throughout all aspects of the trial. The principal investigators, healthcare providers, case managers and study personnel will assist the study monitor by providing all appropriate documentation and being available to discuss the study.

## 23.5 Site close-out

At the completion of the trial, a final monitoring and close out visit will be conducted by the study monitor.

## 23.6 Source documents

The study monitor will check the source documents to confirm the existence of the participant and the integrity of the study data. Source documents refer to the Distress Thermometer self-report tool used by the case managers, and any electronic medical records of the participants used by the healthcare providers during episodes of care related to the study. Adequate and accurate source documents allow the principal investigators and the study monitor to verify the reliability and authenticity of data recorded on the electronic case report forms and ultimately to validate that the study was carried out in accordance with the protocol.

## 23.7 Direct access to data and documents

The study may be audited by the RVH Research Ethics Board, or qualified representatives of the RVH Research Institute as permitted by regulations. Therefore, access to medical records, other source documents and other study related files will be made available at all study sites for monitoring and audit purposes during the study and after its completion.

Participants will not be identified by name, and confidentiality of information in medical records will be preserved. The confidentiality of the participant will be maintained unless disclosure is required by regulations.

# 24 Ethics approval

This protocol and appendices will be reviewed and approved by the RVH Research Institute and the Clinical Trials Ontario-accredited RVH Research Ethics Board with respect to scientific content and compliance with applicable research and human subjects’ regulations.

The protocol, informed consent form, participant education and recruitment materials, and other requested documents, and any subsequent modifications, also will be reviewed and approved by the RVH Research Ethics Board.

Subsequent to initial review and approval, the RVH Research Ethics Board will review the protocol at least annually. The Principal investigators will make progress reports to the RVH Research Ethics Board at least annually and within three months of study termination. These reports will include the total number of participants enrolled, completed the study, in follow-up, lost-to-follow-up, and withdrawn; protocol and informed consent deviations and modifications; and if applicable, total number of adverse events.

# 25 Protocol amendments

Any modifications to the protocol which may impact on the conduct of the study, potential benefit of the participant or may affect participant safety, including changes of study objectives, study design, participant population, sample sizes, study procedures, or significant administrative aspects will require a formal amendment to the protocol. Such amendments will be agreed upon by the Principal investigators, the RVH Research Institute, and approved by the RVH Research Ethics Board prior to implementation.

Administrative changes of the protocol are minor corrections and/or clarifications that have no effect on the way the study is to be conducted. These administrative changes will be agreed upon by the Principal investigators, the RVH Research Institute, and will be documented in a Note to File to the RVH Research Ethics Board.

# 26 Consent

This study fulfils the criteria for a low-risk intervention trial in that the study interventions and study-related assessments and follow-up pose no more than minimal additional risk or burden to the safety of the participants. As such, all eligible participants will be briefly informed by their case managers about the main features of the trial during their TDTP orientation session. This introduction will include information about randomisation, the Distress Thermometer self-report tool, support pathways for MH&A, study-related questionnaires and follow-up. For those participants who are interested in learning more about the study, they will be provided with the contact information for study personnel (Section 15). After contacting the study personnel, the informed consent process will be administered as described previously in Section 15.

# 27 Confidentiality

All participant data pertaining to the study will be stored in a computer database maintaining confidentiality in accordance with PHIPA regarding privacy and use of health data. When archiving or processing data pertaining to the investigators and/or to the participants, the RVH Research Institute will take all appropriate measures to safeguard and prevent access to this data by any unauthorized third party.

The investigators will maintain the confidentiality of all study documentation and take measures to prevent accidental or premature destruction of these documents. After the completion or discontinuation of the study the investigators will retain the study documents

ten (10) years in Canada as required by regulation. The investigators must notify the RVH Research Institute prior to destroying any study documents following study completion or discontinuation. If the investigators’ situation is such that archiving can no longer be ensured, the investigators will inform the RVH Research Institute, and the relevant records will be transferred to a mutually agreed designee.

If any of the investigators retire, relocate, or otherwise withdraw from conducting the study, the responsibility for maintaining records may be transferred to the RVH Research Institute or another investigator. The RVH Research Institute must be notified of and agree to the change. All associated documentation must also be updated.

# 28 Declaration of interests

GD and CS have never received any salary support or grants, honoraria, paid consultancies or service on advisory boards, receipt of patents or patents pending, ownership of stocks or options from Community Builders Construction or Alectra. SB is a paid employee of Community Builders Construction. Community Builders Construction has received a Federal grant from the Youth Employment and Skills Strategy program.

# 29 Access to data

The RVH Research Institute will oversee the intra-study data sharing process. The Principal Investigators will be given access to the cleaned data sets. Study data sets will be housed on the RVH REDCap web-site created for the study, and all data sets will be password protected. The Principal Investigators will have direct access to the data sets. To ensure confidentiality, any data dispersed to the study healthcare providers, case managers or study personnel will be de-identified participant information and aggregated whenever feasible.

# 30 Post-trial care

Should this study provide evidence of the superior effectiveness of using the Distress Thermometer and/or MH&A care pathways compared to usual case management, subsequent TDTP or similar construction vocational programs administered by Community Builders Construction will incorporate similar case management strategies.

# 31 Trial results and authorship

The study will be conducted in the name of the ‘TeachMeToBuild Trial Investigators’. Overall project coordination and data management will be provided by the RVH Research Institute. Study results will be disseminated via abstracts, trial registry, journal publication and RVH Research Institute and Community Builders Construction and Alectra websites regardless of the magnitude or direction of effect.

Authorship of publications arising from the study will be consistent with current International Committee of Medical Journal Editors’ recommendations (<http://www.icmje.org/recommendations/>) with full credit assigned to all collaborating investigators, healthcare providers, study personnel and corporations. Responsibility for the content of manuscripts will rest with the Principal Investigators, and where listed, [name] will be listed as first author, [name] will be listed as second author, and [name] will be listed as corresponding author, with all other subsequent members listed alphabetically following [name] and preceding [name].

Funding bodies will be acknowledged in all publications.

